#### Dropout Criteria

All participants who signed the informed consent and were eligible for observation but did not complete the observation period for any reason will be considered dropouts.

### Interventions

#### Guideline-Based Surveillance

Both groups will receive guideline-based surveillance for pulmonary nodules, including thin-slice chest CT follow-up, clinical evaluation, and referral for diagnostic work-up, surgery, or oncologic treatment when clinically indicated. The study intervention is not a substitute for standard care. If lung cancer is suspected or confirmed during follow-up, the participant will be managed according to contemporary clinical guidelines and local multidisciplinary recommendations; such events will be recorded as trial outcomes.

#### YFSJ Optimized Formula Granules

Participants allocated to the experimental group will take optimized YFSJ formula granules—2 packets per dose, dissolved in hot water—twice daily for 6 months. The source formula is composed of 8 herbs as described in Table 1; the crude-drug equivalent dose and the final granule extraction ratio or packet weight should be verified against the investigational product specification.

**Table 1. T1:** Composition of the Yifei Sanjie Pill (YFSJ) source formula^a^.

Number	Herbal component	Latin or pharmaceutical name	Crude-drug equivalent in source formula, g
1	Sarcandra glabra	*Sarcandra glabra* (Thunb.) Nakai	15
2	Bombyx batryticatus	Bombyx batryticatus	10
3	*Ranunculus ternatus*	*Ranunculus ternatus* Thunb.	30
4	*Iphigenia indica*	*Iphigenia indica* Kunth	15
5	Fritillaria bulb	Bulbus *Fritillariae thunbergii*	15
6	*Pinellia ternata*	*Pinellia ternata* (Thunb.) Breit.	15
7	*Ganoderma lucidum*	*Ganoderma lucidum* (Leyss. ex Fr.) Karst.	30
8	American ginseng	*Panax quinquefolius* L.	15

a The investigational granules are manufactured by Jiangyin Tianjiang Pharmaceutical Co, Ltd. The batch number, quality-control fingerprint, heavy metal or pesticide testing, granule extraction ratio, and gram weight per packet will be recorded in the trial master file.

#### Placebo Granules

Participants allocated to the control group will take matched placebo granules—2 packets per dose, dissolved in hot water—twice daily for 6 months. The placebo contains 5% of the active YFSJ optimized granules, along with flavoring agents, starch, and colorants to match the appearance, taste, smell, packaging, and administration schedule as closely as possible. The placebo is used only in addition to guideline-based surveillance and does not withhold clinically indicated care.

#### Concomitant Medication Rules

All concomitant medications and treatments during the trial period (screening and treatment period) must follow the following rules:

In addition to the study medication, doctors should require patients to bring all medications they are taking to follow-up visits for checking. Essential medications or other treatments for concomitant diseases should be recorded in the case report form (CRF), including the medication name (or other treatment), dosage, frequency, and timing for analysis and reporting.Patients may receive necessary treatment for other diseases or symptoms (unrelated to this condition), but the treatment must be truthfully and thoroughly recorded in the CRF.During the trial, the use of other TCM prescriptions with known antitumor activity or with primary functions such as fever reduction (antipyretic), phlegm clearance (mucolytic), and lung function support (including bronchodilatory effects) is prohibited.

#### Randomization, Allocation Concealment, and Blinding

The random allocation sequence will be generated by an independent third-party statistician using a computer-based random number generator. Participants will be randomized in a 1:1 ratio to the YFSJ or placebo group. Allocation concealment will be maintained using sequentially numbered, sealed, and opaque envelopes or an equivalent centralized allocation procedure; the sequence will not be available to investigators responsible for the enrollment or outcome assessment.

The trial uses a double-blind design. Participants, treating clinicians, investigators, outcome assessors, data managers, and statisticians will remain blinded to group assignment until database lock, except in medical emergencies requiring unblinding. Study medications will be identical in packaging and labeled by coded box numbers. Emergency unblinding procedures will be documented, and the reason, date, and person performing the unblinding will be recorded.

### Outcome Measures and Rationale

#### Clinical Efficacy Outcomes

The outcomes were selected to evaluate YFSJ across 4 levels: (1) lesion-level clinical efficacy, using objective nodule progression as the primary end point; (2) imaging-based quantitative change, including CT and AI-derived size, volume, and malignancy risk; (3) patient-reported symptoms, psychological distress, and sleep quality, reflecting the burden of long-term surveillance; and (4) exploratory biological mechanisms that may link the TCM phlegm-heat-toxin pattern with measurable inflammatory, immune, metabolic, and endoplasmic-reticulum (ER) stress pathways. This hierarchy ensures that the trial hypothesis remains centered on disease progression while allowing secondary and mechanistic analyses.

#### Primary End Point

The primary outcome is the 2-year lung nodule progression rate. Progression of a ground-glass nodule is defined as an increase in the longest diameter of the lesion by ≥2 mm, an increase in the solid component by ≥1 mm, or the appearance of a new solid component. When multiple nodules are present, the largest or clinically dominant nodule will be used for primary assessment, and changes in other nodules will be documented as supportive information.

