### Case Selection

#### Sample Size Estimation

This trial uses the 2-year disease progression rate of pulmonary nodules as the primary end point. Previous studies have reported a 2-year progression rate of ≤8 mm mixed ground-glass nodules at approximately 24% [19]. Assuming a 2-year progression rate of 14% in the intervention group, with 80% power, a 5% false-positive error rate (2-sided), and a dropout rate controlled within 20%, a total of 596 participants need to be enrolled. The trial will include 600 patients, with 300 in the experimental group and 300 in the control group (Figure 1).

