#### Termination or Withdrawal Criteria

Participants will be withdrawn from the study or have their treatment discontinued if any of the following conditions occur:

Patients experiencing severe adverse events (life-threatening or significantly impacting normal daily work and life) will discontinue treatmentPatients experiencing severe and persistent allergic reactions will cease treatment and be considered ineffective casesPatients unwilling or unable to continue clinical trials for any reason and requesting withdrawalPatients who undergo other treatments, such as surgery, without disease progression will be considered censored casesSignificant protocol violations (adherence <80% or >120%)

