### Statistical Analysis

Data will be collected at baseline and during follow-up visits using standardized CRFs. Key data include demographics, clinical history, imaging findings (chest CT and AI-assessed nodule features), laboratory results (tumor markers, blood, urine, stool, liver and kidney function, and ECG tests), and patient-reported outcomes (TCM symptom scale, provided in Multimedia Appendix 1, HADS, and PSQI). To ensure data quality, assessors will receive uniform training, and duplicate measurements will be conducted where appropriate. All instruments used have been validated in prior clinical practice. Data collection forms are included in the protocol and managed through an EDC system.

Based on the actual number of participants enrolled in the 2 groups, dropout and exclusion cases, as well as demographic and other baseline characteristics, corresponding efficacy and safety analyses will be conducted. Descriptive statistical analysis will be used, with qualitative indicators described as frequency tables, percentages, or proportions; quantitative indicators will be described as mean (SD), median (IQR), and minimum and maximum values.

For primary end points and clinical efficacy analysis, the main and sensitivity analyses will be performed according to the full analysis set and per-protocol set, respectively. Safety analysis will be conducted using the safety set. The main analysis of the primary end point will use the log-rank test to compare the 2-year progression rates between groups, with Cox regression adjusting for covariates (eg, center) as a sensitivity analysis. Subgroup analyses will be conducted based on the center and whether >8 mm nodules were surgically removed. The malignancy risk index, quality-of-life scores at different time points, and other multiple measurement indicators will be analyzed using mixed-effects models. Eligibility-related protocol deviations, including any deviations from the retained immune disease exclusion criterion, will be documented. Participants with major eligibility deviations will be handled according to the prespecified analysis-set definitions, with sensitivity analysis based on the per-protocol set. Safety end points will summarize adverse reactions and events occurring during the study and compare rates between groups. Hypothesis testing will uniformly use 2-sided tests, providing test statistics and corresponding *P* values, with *P*<.05 considered statistically significant.

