## Discussion

### Principal Findings

This trial is designed to test the hypothesis that YFSJ, when added to guideline-based surveillance, can reduce the 2-year progression rate of high-risk pulmonary nodules compared with placebo combined with the same surveillance strategy. If the intervention reduces progression without increasing adverse events, YFSJ may provide a noninvasive adjunctive option for patients with small, high-risk, and mixed ground-glass nodules who do not yet meet the criteria for invasive treatment.

The primary end point is objective radiologic progression. Patient-reported psychological and sleep outcomes are included because prolonged surveillance may create distress, and symptom improvement is relevant to integrative care; however, these outcomes will be interpreted as secondary and supportive.

Existing pulmonary nodule guidance focuses on risk stratification, CT follow-up, and surgical or diagnostic intervention when features suggest malignancy [4-6]. Recent AI-based studies further show that integrating quantitative imaging, clinical features, and longitudinal data can refine malignancy risk classification [8,9]. However, these approaches mainly improve detection and decision-making; they do not provide pharmacological prevention of nodule progression.

YFSJ has been studied in non–small cell lung cancer models and adjunctive treatment settings, with evidence suggesting regulation of apoptosis, autophagy, and inflammatory pathways [14-18]. While those studies focused on established lung cancer, this trial extends this prior work to a prevention-oriented population with high-risk pulmonary nodules, using a randomized, double-blind, and placebo-controlled design to reduce bias.

Key strengths of this study include the multicenter, randomized, double-blind design; matched placebo control; objective 2-year radiologic primary end point; standard-of-care surveillance in both groups; AI-assisted quantitative imaging; patient-reported outcomes; and planned exploratory plasma analyses. The trial also explicitly distinguishes clinical efficacy end points from mechanistic hypotheses, which improves interpretability.

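### Severe and persistent allergic reactions are labelled ineffective cases, a status that the CT-only primary end point has no place for and that could be coded as progression

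*Protocol article*

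**What the plan says.** Primary End Point (Methods) gives three CT criteria and nothing else. The first reads: "Progression of a ground-glass nodule is defined as an increase in the longest diameter of the lesion by ≥2 mm". The other two are solid-component growth of at least 1 mm and a new solid component. The Abstract repeats this definition, and the Discussion (Principal Findings) confirms its nature: "The primary end point is objective radiologic progression".

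Termination or Withdrawal Criteria handles three clinical events in three ways:

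- Participants "experiencing severe adverse events (life-threatening or significantly impacting normal daily work and life) will discontinue" treatment. No outcome status is attached.
- Participants "experiencing severe and persistent allergic reactions will cease treatment and be considered ineffective" cases.
- Participants "who undergo other treatments, such as surgery, without disease progression will be considered censored" cases.

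Statistical Analysis states: "The main analysis of the primary end point will use the log-rank test to compare the 2-year progression rates between groups". The main analysis uses the full analysis set, with the per-protocol set as a sensitivity analysis. That section does not mention ineffective cases.

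Placebo Granules adds: "The placebo contains 5% of the active YFSJ optimized granules", together with flavoring agents, starch and colorants.

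**The concern.** The list of termination criteria mixes two things: when treatment stops, and what status a participant then has in the analysis. Censoring is a status in a time-to-event analysis, and the only such analysis described is that of progression. Next to it, the ineffective label also reads like an outcome assignment. If stopping treatment were all that was meant, the wording used for severe adverse events would have been enough.

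None of the listed secondary end points is an effective/ineffective classification. A programmer who follows the termination criteria may therefore code these participants as failures on the primary end point. One who follows the Primary End Point section would not, unless a CT criterion is met. Under the first coding, the reported progression rate would include people whose nodules did not grow, and a drug reaction would count once as a safety event and again as an efficacy failure. If reactions are commoner on the full-strength product, the comparison would shift against YFSJ.

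**Working it through.** **1. The passages side by side.** Take a participant with a severe and persistent allergic reaction and stable CTs to month 24. Under the Primary End Point section this is not an event. Under the termination criteria the participant is ineffective. The log-rank test needs an event indicator and a time, and the article does not translate the label into either. Both sections can be obeyed only if the label has no role in the primary analysis, and the article does not say so.

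**2. Reproducing the planned sample size.** Inputs from Sample Size Estimation: control rate 24% ("Previous studies have reported a 2-year progression rate of ≤8 mm mixed ground-glass nodules at approximately 24"%), YFSJ rate 14%, 80% power, two-sided 5%, 20% dropout.

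n per arm = (1.960 + 0.842)² × (0.24 × 0.76 + 0.14 × 0.86) / 0.10² = 7.849 × 0.3028 / 0.01 = 237.7, so 238.

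With dropout: 238 / 0.80 = 297.5, so 298 per arm and 596 in total. This matches the article exactly. The sample size is not in error.

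**3. Illustration of the effect on power.** The article gives no rate of severe and persistent allergic reactions. Assume that a share k of the YFSJ arm has one, that none occur on placebo, and that 86% of those affected would not otherwise have progressed. Coded as events:

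YFSJ rate = 0.14 + 0.86 × k

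Power = Φ(difference / SE − 1.960), with SE = √[(p₁(1 − p₁) + p₂(1 − p₂)) / n]

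For k = 1% at 238 per arm: YFSJ rate 0.1486, difference 0.0914, SE 0.0360, ratio 2.537, power Φ(0.577) = 0.718.

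| Excess in YFSJ | YFSJ rate | Power, 238 per arm | Power, 300 per arm |
|---|---|---|---|
| 0 | 14.0% | 80% | 88% |
| 1% (3 of 300) | 14.9% | 72% | 81% |
| 2% (6 of 300) | 15.7% | 62% | 72% |
| 3% (9 of 300) | 16.6% | 52% | 62% |

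**4. Equal rates in both arms.** With 2% in each arm, the control rate becomes 0.24 + 0.76 × 0.02 = 25.5% against 15.7%. Power is 76% at 238 per arm and 85% at 300. Most of the loss in step 3 therefore comes from imbalance between arms.

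**The case against.** The strongest reply is that the label is ambiguous rather than contradictory. The termination criteria never use the words event or progression for these participants, and under the Primary End Point and Statistical Analysis sections a participant without CT growth is not an event. The list is a mixed one, so survival terminology in one bullet does not prove that another bullet feeds the log-rank test. The label could be leftover wording or belong to some other efficacy summary, and event coding normally sits in an analysis plan that is not shown. This stands to a point: a reader might infer that ineffective can only mean an event, or that safety events will definitely be counted as progression. The article does not establish either. But it does state the rule, so this is more than detail left to another document, and an analysis plan would still have to choose between the two sections.

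A second reply is that counting treatment failure as an event is a recognised composite strategy, and that a bias against YFSJ would not create a false claim of efficacy. Both are true in general. This trial, however, describes its end point as objective radiologic progression, and a composite is not that.

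The third reply concerns size, and it stands. The rule covers only reactions that are both severe and persistent, known allergy to the components is an exclusion criterion, and placebo has its own excipients and some active product. A concentration of reactions in the YFSJ arm is an inference from the 5% placebo content, not something the article reports. With all 300 per arm evaluable, a 1% excess still leaves power above the 80% target. A single reactor among 300 lowers power at 238 per arm only from 80% to about 77%. Reading the 62% or 52% figures as expected losses would be unsupported: they need six or nine such reactions in one arm and none in the other.

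**Conclusion.** The concern holds as an unreconciled status rule. The termination criteria give an efficacy label to a safety event, while the primary end point is defined by CT alone and has no place for that label. If it is coded as an event in the full-analysis-set comparison, non-progressors would count as progressors, and the estimate would plausibly be biased against YFSJ.

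The size cannot be fixed from the article. It depends on how often these reactions occur and how unevenly they fall between the arms, and probably few participants are affected. The power figures are illustrations under the stated assumptions, including the most adverse one of no reactions on placebo. The point deserves correction because the meaning of the primary result depends on it and the remedy is simple. It does not show that the analysis will go wrong.

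**What to change.** Reconcile Termination or Withdrawal Criteria, Primary End Point and Statistical Analysis before database lock, which is planned for early 2028:

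- Remove the ineffective label from the primary analysis and state that event status is set by the CT criteria alone.
- Keep these participants in the full analysis set, with the CTs already scheduled at months 6, 12, 18 and 24 where consent permits. Otherwise censor at the last CT.
- Analyse the reaction as a safety event.
- If a treatment-failure analysis is wanted, label it supplementary.

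When treatment stops is a clinical matter and is not addressed here.

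The cost is a short protocol amendment. Recruitment began in June 2023, so CTs already missed by participants who have been withdrawn cannot be recovered. The change should be made while the statisticians are still blinded, so that the coding is not chosen after the results are known.

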#### Secondary End Points

The following secondary end points will be assessed:

Lung cancer detection rate during the 2-year follow-up, confirmed by histopathology when available or by multidisciplinary clinical diagnosis when pathology is unavailableSurgery rate and reason for surgery, including progression, patient preference, suspected malignancy, or other clinical indicationsThe 6-month change in nodule size, solid-component size, CT density, and AI-derived nodule volumeAI malignancy risk index, defined as the algorithm-generated malignancy probability or risk score for the target nodule. The score scale will be reported according to the software output, typically 0 to 100 or a calibrated probability, with higher values indicating higher predicted malignancy risk. The AI system is an independently developed deep learning–based automatic lung nodule segmentation technology (patent application number: 202510952658.0)Pulmonary nodule symptom scale, based on the trial-specific TCM symptom scale for cough, sputum, chest tightness, fatigue, dry mouth or throat, heat signs, and other symptoms related to the phlegm-heat-toxin pattern. This scale was developed using the Delphi expert consensus method to provide a standardized symptomatic evaluation tool for pulmonary nodule patients treated with TCM or integrated traditional Chinese and Western medicine interventions. Each item, scoring range, and minimal clinically important difference will be listed in the final protocol appendix [20]HADS, a 14-item instrument with anxiety and depression subscales [21]PSQI, a validated self-report measure of sleep quality [22]

#### Safety Outcomes

The following safety outcomes will be assessed throughout the study:

Vital signs, including pulse, respiratory rate, blood pressure, and temperatureBlood routine, liver function, kidney function, urinalysis, stool examination, and electrocardiogram ()All adverse events and serious adverse events, including onset date, duration, severity, relationship to study medication, action taken, outcome, and whether unblinding was required

### AI-Assisted CT Assessment

Chest CT will be performed using a thin-slice protocol harmonized across participating centers as far as feasible. CT acquisition parameters, reconstruction kernel, slice thickness, and scanner model will be recorded. Radiologists, blinded to treatment allocation, will assess nodule type, longest diameter, solid-component size, morphology, and progression status.

The AI-assisted nodule analysis system, an independently developed deep learning–based automatic lung nodule segmentation technology (patent application number: 202510952658.0), will segment the target nodule and extract quantitative features, including nodule volume, longest diameter, solid-component size, density, and malignancy risk index. The AI output will not replace clinical judgment or standard reporting. Discrepancies between radiologist assessment and AI output will be reviewed by a blinded adjudication committee or a senior radiologist according to a prespecified adjudication procedure.

### Follow-Up and Data Collection

Baseline data will include demographics, smoking history, comorbidities, prior cancer history, medication history, physical examination, vital signs, blood routine, liver function, kidney function, urinalysis, stool examination, tumor markers, ECG, chest CT, AI-derived nodule variables, TCM symptom score, HADS, and PSQI. Follow-up visits will occur at 3 and 6 months during the intervention period and every 6 months thereafter until nodule progression, surgery, withdrawal, death, loss to follow-up, or study completion. The trial protocol is version 3.0 (March 20, 2023), and the schedule of study procedures is shown in Table 2.

**Table 2. T2:** Schedule of study procedures, assessments, and follow-up visits.

Procedure	Screening/baseline	Randomization	Month 3	Month 6	Month 12	Month 18	Month 24/ end point
Eligibility	✓						
Consent	✓						
Demog.^a^	✓						
Random.^b^		✓					
Study drug		Start	Continue	End			
Meds^c^	✓	✓	✓	✓	✓	✓	✓
Vitals or AEs^d^	✓		✓	✓	✓	✓	✓
Labs or ECG^e^	✓		✓	✓	As indicated	As indicated	✓
CT^f^	✓			✓	✓	✓	✓
AI^g^	✓			✓	✓	✓	✓
TCM^h^ symptoms	✓		✓	✓	✓	✓	✓
HADS^i^ or PSQI^j^	✓		✓	✓	✓	✓	✓
Plasma	✓			✓			Optional or if specified
End point							✓

a Demog.: demographics and medical history.

b Random.: randomization and dispensing.

c Meds: concomitant medication review.

d AEs: adverse events.

e ECG: electrocardiogram.

f CT: computed tomography.

g AI: artificial intelligence.

h TCM: traditional Chinese medicine.

i HADS: Hospital Anxiety and Depression Scale.

j PSQI: Pittsburgh Sleep Quality Index.

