## Abstract

**Background:**

High-risk subsolid pulmonary nodules, especially mixed ground-glass nodules, can represent precancerous or early-stage lung adenocarcinoma spectrum lesions. Standard management relies mainly on risk stratification, repeated thin-slice computed tomography, and invasive diagnosis or surgery when progression suggests malignancy. Safe adjunctive pharmacologic options to reduce nodule progression remain limited. Yifei Sanjie Pill (YFSJ) is an 8-herb traditional Chinese medicine formula that has been previously studied as an adjunctive treatment for non–small cell lung cancer. However, its effect on high-risk pulmonary nodules—a distinct clinical condition—has not yet been investigated.

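### Scheduled follow-up ends at nodule progression, so lung cancer diagnoses and operations that come after progression are not systematically counted, and more of them are lost in the arm that progresses more

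*Protocol article*

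**What the plan says.** All places are in the Protocol article.

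- **Follow-Up and Data Collection** sets visits at 3 and 6 months, then "every 6 months thereafter until nodule progression, surgery, withdrawal, death, loss to follow-up, or study completion". Table 2 merges month 24 with the end-point visit in its last column, which fits an early final visit for a participant who progresses.
- **Secondary End Points** includes "Lung cancer detection rate during the 2-year follow-up, confirmed by histopathology when available", or by multidisciplinary diagnosis where there is no pathology. It also includes a surgery rate with the reason for surgery. Progression and suspected malignancy are among the listed reasons. No time window is given for the surgery rate.
- **Abstract, Background** describes usual management as CT surveillance, with "invasive diagnosis or surgery when progression suggests malignancy".
- **Guideline-Based Surveillance** says "If lung cancer is suspected or confirmed during follow-up, the participant will be managed according to contemporary clinical guidelines", and that "such events will be recorded as trial outcomes".
- **Adherence and Retention Strategies** covers missed visits and data collection at withdrawal. It does not mention participants whose visits have ended because of progression.

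**The concern.** The stopping rule suits a time-to-progression primary endpoint but not these two secondary endpoints. An operation for progression can only take place at or after progression, when the participant has no further trial visits. The same holds for a diagnosis made in the work-up that progression prompts. The sentence about recording cancers as outcomes is limited to those arising during follow-up, and the stopping rule ends follow-up at progression.

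The loss depends on the treatment effect under test. If YFSJ reduces progression, more placebo participants leave early and more placebo events go uncounted. A real reduction in cancers or operations would then look smaller than it is. Analysis cannot repair this, because the data would not have been collected.

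**Working it through.** **1. The plan's own sample size.** Inputs from Sample Size Estimation: 24% on control, "Assuming a 2-year progression rate of 14% in the intervention group", two-sided 5%, 80% power, 20% dropout. With the unpooled two-proportion formula:

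n per arm = (0.24×0.76 + 0.14×0.86) × (1.960 + 0.842)² / 0.10² = 0.3028 × 7.849 / 0.01 = 237.7, rounded up to 238.

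238 / 0.8 = 297.5, rounded up to 298 per arm, or 596 in total. This matches the stated figure. The sample size is not in dispute; it supplies the planned number of progressors.

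**2. Participants who reach the stopping rule by progression.** With 300 per arm and no dropout: 300 × 0.24 = 72 on placebo and 300 × 0.14 = 42 on YFSJ, 114 of 600 in total (19%).

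**3. How many lose time inside the 24 months.** Progression first seen at month 24 costs nothing within the window. Assume a constant hazard, S(t) = (1 − p)^(t/24), and detection at the CT visits in Table 2. The expected number first detected at a visit is 300 × [S(t − 6) − S(t)].

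| CT visit | Months lost | Placebo (p = 0.24) | YFSJ (p = 0.14) |
|---|---|---|---|
| 6 | 18 | 19.9 | 11.1 |
| 12 | 12 | 18.6 | 10.7 |
| 18 | 6 | 17.3 | 10.3 |
| 24 | 0 | 16.2 | 9.9 |

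Detected before month 24: 19.9 + 18.6 + 17.3 = 55.8, about 56 on placebo; 11.1 + 10.7 + 10.3 = 32.1, about 32 on YFSJ. That is 88 of the 114, each stopped 6 to 18 months early.

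**4. Operations that could be missed.** The documents give no figure for surgery after progression. Assume 30-70% of these 88 have surgery by month 24, the same share in both arms, and that none is captured.

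- Placebo: 56 × 0.3 = 16.8 and 56 × 0.7 = 39.2, so 17-39.
- YFSJ: 32 × 0.3 = 9.6 and 32 × 0.7 = 22.4, so 10-22.
- Arm difference lost: (56 − 32)/300 = 8.0 points; × 0.3 = 2.4 and × 0.7 = 5.6 points.

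**5. Effect of dropout.** If 20% dropout falls evenly across progressors, the counts in step 3 shrink to about 56 × 0.8 = 45 and 32 × 0.8 = 26. The imbalance between arms remains.

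**The case against.** The best reply is that the stopping sentence governs visits, not ascertainment. Guideline-Based Surveillance says cancers will be recorded as outcomes, and listing progression as a reason for surgery shows that the trial means to count such operations. The full protocol, version 3.0, is not shown and may describe retrieval from records. Part of this stands. The intention is clear, and work-up or surgery arranged around the progression visit may well be captured. But the article states a stopping rule and an endpoint window that do not fit together, and no section provides contact after progression. This is a conflict in the stated text, not a detail left out.

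A reader might infer more than the documents support:

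- **That these endpoints cannot be observed at all, or that most such events come from progressors.** Some events will be captured, and no figure is given for the share that follows progression.
- **That all 114 progressors lose follow-up time.** Under a constant hazard about 26 are first detected at month 24 and lose none within the window.
- **That a real benefit could be reversed.** Take an extreme illustration: 1% cancer detection in non-progressors, 20-60% in progressors, and nothing captured in any progressor. The true difference of 1.9-5.9 points becomes 0.76 × 1% − 0.86 × 1% = −0.1 points. That is loss of the difference, not a meaningful reversal.
- **That both endpoints carry a 2-year window.** Only lung cancer detection does.
- **That false-positive progression would go unchecked.** Readers are blinded, discrepancies between radiologist and AI output are adjudicated, and clinical surveillance continues. Record checks would add no trial scan in any case.
- **That every repeated outcome is compromised.** The 6-month imaging changes and the month-6 plasma sample fall at the first scheduled follow-up CT and should rarely be affected. Whether questionnaires are wanted after progression depends on the question asked of them.

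**Conclusion.** The point holds as a conflict between the visit-stopping rule and two secondary endpoints. Followed as written, the plan does not systematically ascertain cancer diagnoses and operations after progression, and the gap is wider in the arm with more progression. The bias is toward no difference.

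The counts of about 56 and 32 rest on the planning rates, no dropout, a constant hazard and detection at scheduled CT. The 2.4-5.6 points further assume 30-70% surgery in both arms and no capture at all, so they are an upper bound for that range. Any capture through clinical contact reduces them. If YFSJ had no effect on progression, the truncation would be expected to be equal between arms.

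Stopping visits at the primary event does not affect the primary endpoint, its log-rank test or the sample size. That limits the severity: this should be fixed, but it does not threaten the main result.

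**What to change.** Reconcile Guideline-Based Surveillance, Secondary End Points, and Follow-Up and Data Collection as follows:

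- Progression or surgery ends only the primary-endpoint clock.
- Surgery with its reason, pathology or multidisciplinary diagnosis, and vital status are ascertained to month 24 in all randomised participants, by phone and medical records.
- The same information is retrieved retrospectively, as consent permits, for those whose visits have already stopped.
- The surgery rate is given a 24-month window, and both rates are analysed over 24 months in all randomised participants.

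The cost is a short amendment and phone or record checks for roughly 90-115 participants (88 to 114 in the working). No additional CT is needed. Phone contact is already part of the retention procedures. Recruitment began in June 2023 and the last primary end-point visit is scheduled for December 2027, so there is still time. Retrieval becomes harder for participants who stopped earliest, so the change is better made soon.
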